##### Outcomes

The outcomes of the study will include the following:

1. Prevalence of colorectal cancer and advanced colorectal neoplasia in patients with CKD

2. Screen positivity rate: defined as the proportion of participants with positive screens in the total screened study population

3. Test sensitivity: defined as the number of colorectal cancers and/or advanced neoplasms detected through screening divided by the total number of colorectal cancers and/or advanced neoplasms detected through screening and the total number of cancers and/or advanced neoplasms occurring within the delay in a given period (the follow-up time) after a negative screen.

4. Test specificity: defined as the number of participants with no colorectal cancers and/or advanced neoplasms within the follow-up period divided by the number of participants with no colorectal cancers and/or advanced neoplasms after a negative screen and the number of participants without colorectal cancers and/or advanced neoplasms after a positive screen within the follow-up period.

5. Participation rate of screening among individuals with CKD.

6. Potential harms of screening and the diagnostic colonoscopies, such as bleeding, bowel perforation and the inherent risks of peritonitis, particularly among peritoneal dialysis patients.

7. Direct healthcare costs, including individually- collected screening, diagnostic, treatment and overhead costs.

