##### Statistical analyses and sample size calculations

Sensitvity and specificity of iFOBT screening for advanced colorectal neoplasia and cancer will be estimated for (i) CKD (stages 3-5) patients, (ii) dialysis patients, and (iii) transplant patients. For each estimate, the required sample size will be determined by the combined expected prevalence of advanced neoplasia and cancer, the expected sensitivity and specificity, and the required precision of the estimated maximum 90% confidence interval width. For each of the three patient groups, the sensitivity is expected to be 75% and the maximum required 90% confidence interval width is ± 10%. Therefore, 51 cases of advanced neoplasms and cancer will be required. The total sample size and the precision of the estimates of specificity (which is expected to be 90%) for each patient group will be determined by the expected prevalence for that group. In the CKD stages (3-5) group (with a one-year combined estimated prevalence of disease equals to 3.1%), a total of 1637 patients would yield 51 cases and 1586 non-cases. The maximum 90% confidence interval width for specificity is ± 1.3%. Among those on dialysis (with a one-year combined prevalence of disease equals to 3.94%), a total of 1288 patients would yield 51 cases and 1237 non-cases, giving a maximum 90% confidence interval width for specificity of ± 1.4%. Assuming a one-year combined prevalence of disease equals to 4.2% in the transplant population, a total of 1208 patients will again yield a total of 51 cases and 1157 non-cases, giving a maximum 90% confidence interval width for specificity of ± 1.5%.

Across all 3 groups, a total of 4133 participants are required over a 5-year screening period. Assuming a participation rate of 68%, a population size of 6077 CKD patients is required to achieve the target sample size of 4133 for any meaningful analyses.

These sample sizes will provide 80% power to detect a difference of between 3% and 4% in specificity between groups of patients. The small number of expected cases does not allow comparisons in sensitivity to be made between groups.

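### The specificity definition omits the negative-screen condition from its numerator, so as written specificity is 100% whatever the test does

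*Protocol article*

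**What the plan says.** Item 4 of the Outcomes list under Study design 1 defines specificity as a ratio. The numerator comes first: "defined as the number of participants with no colorectal cancers and/or advanced neoplasms within the follow-up period divided by the number of participants". The denominator has two terms. The first is introduced by "divided by the number of participants with no colorectal cancers and/or advanced neoplasms after a negative screen"; the second is "the number of participants without colorectal cancers and/or advanced neoplasms after a positive screen within the follow-up period".

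Item 3 of the same list defines sensitivity, and there the numerator is tied to the screen: "defined as the number of colorectal cancers and/or advanced neoplasms detected through screening divided by" the screen-detected disease plus the disease that appears after a negative screen.

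The section on statistical analyses and sample size calculations expects specificity of 90% in each of the three patient groups. It gives maximum 90% confidence interval widths of ±1.3% (CKD stages 3-5, 1586 non-cases), ±1.4% (dialysis, 1237) and ±1.5% (transplant, 1157). It claims 80% power to detect a difference of 3% to 4% in specificity between groups, and states that the small number of cases rules out comparing sensitivity between groups.

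No other section gives a different specificity formula.

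**The concern.** Specificity is the share of disease-free people whom the test calls negative, so the numerator must be limited to negative screens. Item 4 leaves that limit out. The numerator is then every disease-free participant, and the denominator is the same people divided by screen result.

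Three parts of the study depend on this quantity:

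- **Aim 1.** The first aim is test performance. The Background names possible harm to specificity from anticoagulation, platelet defects and immunosuppression as a reason for the study. (It also raises a question about sensitivity with low-dose aspirin, so specificity is not the only characteristic in doubt.) The written ratio could not show such a fall.
- **Group comparison.** Specificity is the only accuracy measure for which the protocol claims power to compare groups. Under the written ratio all groups score the same.
- **Economic model.** Study design 2 takes specificity from this study as an input. A value of 1 would remove colonoscopies after false-positive screens from the modelled costs and harms.

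**Working it through.** **Inputs**, all from the sample size section: expected sensitivity 75% with a 90% interval of ±10%; expected specificity 90%; non-cases 1586, 1237 and 1157.

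**1. Reproduce the plan's figures under the usual definition, TN/(TN + FP).**

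Cases needed for sensitivity: 1.645² × 0.75 × 0.25 / 0.10² = 50.7, rounded up to 51. This matches the protocol.

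Half-width for specificity: 1.645 × √(0.9 × 0.1 / n), where n is the number of non-cases.

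| Group | n | Computed | Stated |
|---|---|---|---|
| CKD stages 3-5 | 1586 | 1.24% | 1.3% |
| Dialysis | 1237 | 1.40% | 1.4% |
| Transplant | 1157 | 1.45% | 1.5% |

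The largest gap is 0.06 of a percentage point and has no bearing here.

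Between-group power: the protocol gives no significance level, so two-sided 5% is assumed. Across the three pairs of groups, with 90% in one of them:

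| Difference | Lower value in the other group | Higher value in the other group |
|---|---|---|
| 3 points | 63-70% (90% v 87%) | 75-81% (90% v 93%) |
| 4 points | 85-90% (90% v 86%) | 95-97% (90% v 94%) |

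This is broadly in line with the stated 80% at a difference between 3% and 4%. The planning section therefore uses the usual definition.

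**2. Apply item 4 as written.**

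- Numerator: disease-free in follow-up, any screen result = TN + FP.
- Denominator, first term: disease-free after a negative screen = TN.
- Denominator, second term: disease-free after a positive screen = FP.
- Ratio: (TN + FP)/(TN + FP) = 1.

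**3. Compare at the planned 90%.**

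| Group | FP expected | Item 4 as written | Usual definition |
|---|---|---|---|
| CKD stages 3-5 | 158.6 | 1586/1586 = 100% | 1427.4/1586 = 90% |
| Dialysis | 123.7 | 1237/1237 = 100% | 1113.3/1237 = 90% |
| Transplant | 115.7 | 1157/1157 = 100% | 1041.3/1157 = 90% |

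The false positives total 158.6 + 123.7 + 115.7 = 398 among 1586 + 1237 + 1157 = 3980 non-cases, and none of them affects the written ratio. If true specificity in the CKD stages 3-5 group were 80%, false positives would be 0.2 × 1586 = 317.2 and the written ratio would still be 1586/1586. With every group at 100%, the half-width from the same formula is 1.645 × √(1 × 0 / n) = 0, and no difference between groups can arise.

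**4. Look for a reading that rescues the sentence.** The division closes the numerator before the negative screen is mentioned, so that condition belongs to the denominator. The reference to the follow-up period sets a time window, not a test result. If the numerator were taken to include disease-free people who enrolled but returned no kit, the ratio would exceed 1, which is not specificity either.

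**The case against.** The strongest reply is that this is a slip of wording and not a choice of analysis. Splitting the denominator by screen result serves a purpose only if its first term is meant to be the numerator, and item 3 shows the correct parallel structure. Specificity is a standard quantity, and the protocol says that design, conduct and reporting follow STARD. The planning figures all assume the usual definition. An analyst who obtained exactly 100% in every group, against an expected 90%, would see the error at once. On this view no bias, loss of power or wrong sample size follows.

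Most of that stands. The intended quantity can be recovered, the sample size does not change, and the contrast of 100% with 90% describes the literal rule rather than a likely distortion of the published result. What does not stand is the inference that the text may be left alone. The article does not leave the definition to another document; it states an explicit formula, and that formula gives a wrong answer if followed. An analysis plan with the usual definition would conflict with it.

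**Conclusion.** The point holds: item 4 is wrong as written. By algebra alone, with no numerical assumption, the ratio equals 1 for any set of screened participants. At the plan's figures the written rule returns 100% in each group where the sample size section expects 90%, and it ignores about 398 expected false positives among 3980 non-cases. The 90% and the counts of non-cases are the protocol's own; the two-sided 5% level enters only the power check, on which the conclusion does not depend. The fault lies in the outcome definition, not in the sample size or the intended estimand. It still needs correcting, because it defines the one accuracy measure the study claims power to compare between groups.

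**What to change.** Replace the numerator in item 4 so that the definition reads: the number of screened participants with a negative screen and no colorectal cancer or advanced neoplasm in the follow-up period, divided by the number of all screened participants with no colorectal cancer or advanced neoplasm in that period. This is TN/(TN + FP) and agrees with the sample size section.

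The cost is one sentence. Design, sample size, data collection and patient care are unchanged, and there is no downside. The edit repairs only the missing condition. It does not say which follow-up period applies, and the Reference standard section mentions clinical follow-up at two years and registry linkage at 2, 5 and 7 years.

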##### Diagnostic procedures

All participants with positive iFOBT screens will be invited to undergo subsequent diagnostic colonoscopies. If polyps are found, polypectomies will be conducted at the time of the diagnostic procedure. If advanced mucosal neoplasia is found, it will be planned for endoscopic mucosal resection (EMR) at a separate procedure. Advanced neoplasia is defined as adenoma with at least one of the following features: 1 cm or more in size, tubulovillous or villous components, or high-grade dysplasia, or any advanced neoplasm 1 cm or more in diameter. EMR is used increasingly frequently for minimally invasive curative resection of benign and early-stage malignant lesions (T1a) throughout the gastrointestinal tract. EMR has the advantage of managing large, sessile polyps in the outpatient setting, which is potentially cost-saving and may improve clinical outcomes in this high risk cohort(36).

All cancers identified will be staged and the participants will be referred to the colorectal surgical and oncology team, depending upon the stage of initial diagnoses. All cancer diagnoses will be reported to the Central Cancer Registry of New South Wales (located within the Cancer Institute of NSW) for all patients with CKD, and the Australia and New Zealand Dialysis and Transplant Registry (ANZDATA) for those on renal replacement therapy (CKD-dialysis and CKD-transplant). The ANZDATA registry is comprehensive database that prospectively collects information on all patients on renal replacement therapy in Australia and New Zealand since 1963. The clinical data includes records of all new cancers except for squamous and basal cell carcinomas. Notification of malignant cancers is a statutory requirement for all health-related institutions in New South Wales. The Central Cancer Registry of New South Wales contains all cancer records and the identifying information for patients diagnosed and treated with cancer within the state of New South Wales since 1972.

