##### Reference standard

Clinical follow-up will be the reference standard for all participants. All participants, with or without screen positive results, will be followed clinically two years after their initial screen. To ensure adequate follow-up and accurate calculation of the screening test performance characteristics of cancer, we will compare our records with that of the Central Cancer Registry (CCR) of NSW through data linkage at 2, 5 and 7 years after the initial screens with the attempt to capture all cancer diagnoses.

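### Screen-positives who never have a colonoscopy are counted as disease-free unless a lesion surfaces, which lowers sensitivity and case yield and, slightly, specificity

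*Protocol article*

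**What the plan says.** All places are in the protocol article, Study design 1.

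- **Diagnostic procedures:** "All participants with positive iFOBT screens will be invited to undergo subsequent diagnostic colonoscopies". No uptake is assumed or required.
- **Reference standard:** "Clinical follow-up will be the reference standard for all participants". Follow-up lasts two years. Linkage to the state cancer registry at 2, 5 and 7 years is made "with the attempt to capture all cancer diagnoses".
- **Outcomes, item 3 (sensitivity):** the ratio starts from "the number of colorectal cancers and/or advanced neoplasms detected through screening divided by the total number of colorectal cancers and/or advanced neoplasms", and the denominator is completed by lesions that occur after a negative screen.
- **Outcomes, item 4 (specificity):** the false-positive part of the denominator is "the number of participants without colorectal cancers and/or advanced neoplasms after a positive screen within the follow-up period".
- **Statistical analyses and sample size calculations:** in each of the three patient groups "the sensitivity is expected to be 75% and the maximum required 90% confidence interval width is ± 10" percentage points. "Therefore, 51 cases of advanced neoplasms and cancer will be required". Prevalence is converted directly into cases. The only allowance for non-uptake is 68% participation in screening.

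**The concern.** The target condition includes advanced neoplasia, which the article defines by size, histology and grade of dysplasia. Those features need endoscopy and pathology. Two years of clinical follow-up and a cancer registry will usually not reveal a silent advanced adenoma. For a positive participant without colonoscopy, the absence of a recorded lesion therefore means that nobody looked, yet the definitions read it as absence of disease.

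Some non-uptake is foreseeable. The Background itself describes higher procedural risk in CKD (cardiovascular events with anaesthesia, peritonitis after polypectomy in peritoneal dialysis), and these risks may differ between the three groups.

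Sensitivity is most exposed. It is the quantity that sets the sample size, and each missed lesion among the positives leaves its numerator. Prevalence falls with it. Study design 2 feeds prevalence, sensitivity and specificity into the economic model, so the error would carry over.

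**Working it through.** **Inputs (sample size section):** sensitivity 75%, specificity 90%, 90% interval, 51 cases per group; non-cases 1586 (CKD 3-5), 1237 (dialysis), 1157 (transplant). Colonoscopy uptake u is not in the document and is an assumption, shown as a range.

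**1. The plan's own figures reproduce.** Cases: 1.645² × 0.75 × 0.25 / 0.10² = 50.7, rounded up to 51. Dividing the unrounded 50.7 by prevalences of 3.1%, 3.94% and 4.2% gives the stated 1637, 1288 and 1208. Specificity half-widths, 1.645 × √(0.9 × 0.1 / non-cases), are 1.24, 1.40 and 1.45 points against the stated ±1.3, ±1.4 and ±1.5.

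**2. Planned 2×2 table, CKD 3-5.** TP = 0.75 × 51 = 38.25; FN = 12.75; TN = 0.9 × 1586 = 1427.4; FP = 158.6. Positives number 196.85, of whom 38.25/196.85 = 19.4% carry a lesion. The same share is 23.6% in dialysis and 24.8% in transplant patients.

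**3. Apply the definitions at uptake u.** Assume that no lesion in an unexamined positive surfaces and that all 12.75 screen-negative cases are found. Then (1 − u) × 38.25 moves from TP to FP:

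- found cases = 38.25u + 12.75
- sensitivity = 38.25u / (38.25u + 12.75)
- specificity = 1427.4 / (1586 + 38.25(1 − u))
- apparent prevalence = found cases / 1637
- N that keeps 51 found cases = 1637 × 51 / found cases

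| Uptake (assumed) | Found cases | Sensitivity | 90% half-width | Specificity | Prevalence | N for 51 found cases |
|---|---|---|---|---|---|---|
| 100% | 51.0 | 75.0% | ±10.0 | 90.0% | 3.12% | 1637 |
| 80% | 43.4 | 70.6% | ±11.4 | 89.6% | 2.65% | 1926 |
| 70% | 39.5 | 67.7% | ±12.2 | 89.4% | 2.41% | 2112 |
| 60% | 35.7 | 64.3% | ±13.2 | 89.1% | 2.18% | 2339 |
| 50% | 31.9 | 60.0% | ±14.3 | 88.9% | 1.95% | 2619 |

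**4. If some lesions surface.** If 25% of the lesions in unexamined positives surface and count as screen-detected, 80% uptake acts like 85%: found cases 45.3, sensitivity 71.8%, specificity 89.7%. The losses shrink by about a quarter. Item 3 does not say whether such a lesion counts as screen-detected, and it is not a lesion after a negative screen either. It may therefore fall outside the sensitivity ratio altogether.

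**5. Limit on the specificity effect.** At 0% uptake all 38.25 true positives become false positives. Specificity is then 1427.4/1624.25 = 87.9% (CKD 3-5), 1113.3/1275.25 = 87.3% (dialysis) and 1041.3/1195.25 = 87.1% (transplant). The losses are 2.1, 2.7 and 2.9 points.

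**6. What a repair has to do, at 80% uptake.** Examined positives number 30.6 with a lesion and 0.8 × 158.6 = 126.88 without; 39.37 are unverified.

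- Dropping the unverified: specificity = 1427.4/(1427.4 + 126.88) = 91.8%, an error of +1.8 points that exceeds the −0.4 it replaces.
- Weighting examined positives by 1/0.8: 30.6/0.8 = 38.25 and 126.88/0.8 = 158.6, which restores 75% and 90% if uptake is unrelated to disease among positives.
- Bounds: with all 39.37 disease-free, sensitivity is 70.6% and specificity 89.6%. With all diseased, sensitivity is 69.97/82.72 = 84.6% and specificity 91.8%. With no surfacing, the definitions as written reproduce the lower bound of both.

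**The case against.** **Non-uptake may be small.** The exclusion criteria remove patients who are not fit for colonoscopy, and no uptake rate appears in the article. This stands in part: the exclusion weakens the procedural-risk argument, but an invitation can still be declined, and the uptake figures above remain assumptions.

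**Follow-up will catch some lesions.** Cancers that surface within two years or through linkage are not false positives. This stands. The exposure is mainly silent advanced neoplasia, and the table is the no-surfacing case.

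**Most unverified positives are classified correctly.** This also stands. At 80% uptake in CKD 3-5, about 39 positives are unverified, of whom about 8 carry a lesion and about 31 to 32 are genuine false positives.

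**A reader might infer that differing uptake would distort the between-group specificity comparison.** The article's figures do not support this. That comparison is powered for 3 to 4 points, while 0% uptake in one group against 100% in another moves specificity by at most 2.9. Transplant at 80% against CKD 3-5 at 100% gives 0.6 points.

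**A reader might also take positive predictive value as the main casualty.** It does scale directly with uptake (19.4% to 15.5% at 80% in CKD 3-5), but it is not a listed outcome.

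**Imputation and weighting are matters for an analysis plan.** That is fair for the details of the method. It does not cover the definitions themselves, which are stated and, if followed, give a biased answer.

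**Conclusion.** The point holds for sensitivity, prevalence and case yield, and to a small degree for specificity. Read together, the invitation to colonoscopy, the universal follow-up standard and the false-positive definition count silent advanced neoplasia in unexamined positives as absence of disease, and the sample size makes no allowance for it. In CKD 3-5 at an assumed 80% uptake, sensitivity loses 4.4 points, about 8 of 51 cases are not found, the ±10 precision target is missed by a little over a point, and specificity loses 0.4 points, well inside its own interval.

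These sizes rest on three assumptions: the uptake, no surfacing of unverified lesions, and complete finding of screen-negative cases. The third matters for direction. Lesions missed among screen-negatives would push sensitivity upwards, so the figures isolate the contribution of unexamined positives and do not predict the net error. It does not follow that every unverified positive is misclassified, or that the group comparison of specificity is invalid.

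**What to change.** - **Reference standard and Outcomes:** state that, for advanced neoplasia, disease status in a positive without a completed colonoscopy is unverified, not absent.
- **Estimation:** obtain sensitivity, specificity and prevalence by inverse-probability weighting or multiple imputation of disease status among positives, within patient group, using the baseline age, sex, comorbidity and medication data. Give best- and worst-case bounds as in step 6. Do not drop unverified positives from the false-positive cell without this correction.
- **Item 3:** state whether a lesion found later in an unverified positive counts as screen-detected.
- **Reporting:** give colonoscopy uptake among positives for each of the three groups.
- **Sample size:** restate expected found cases and sensitivity precision under a declared uptake. At 80% the CKD 3-5 group needs 1926 instead of 1637 to keep 51 found cases; alternatively, the wider interval can be accepted and stated.

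The cost is a change of wording and one added analysis. Intervals become somewhat wider, and the correction assumes that, given the covariates, accepting colonoscopy is unrelated to disease among positives. That assumption could fail if symptoms drive acceptance, which is why the bounds are needed. The correction deals with positives only and leaves the finding of screen-negative lesions as it is.

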##### Statistical analyses and sample size calculations

Sensitvity and specificity of iFOBT screening for advanced colorectal neoplasia and cancer will be estimated for (i) CKD (stages 3-5) patients, (ii) dialysis patients, and (iii) transplant patients. For each estimate, the required sample size will be determined by the combined expected prevalence of advanced neoplasia and cancer, the expected sensitivity and specificity, and the required precision of the estimated maximum 90% confidence interval width. For each of the three patient groups, the sensitivity is expected to be 75% and the maximum required 90% confidence interval width is ± 10%. Therefore, 51 cases of advanced neoplasms and cancer will be required. The total sample size and the precision of the estimates of specificity (which is expected to be 90%) for each patient group will be determined by the expected prevalence for that group. In the CKD stages (3-5) group (with a one-year combined estimated prevalence of disease equals to 3.1%), a total of 1637 patients would yield 51 cases and 1586 non-cases. The maximum 90% confidence interval width for specificity is ± 1.3%. Among those on dialysis (with a one-year combined prevalence of disease equals to 3.94%), a total of 1288 patients would yield 51 cases and 1237 non-cases, giving a maximum 90% confidence interval width for specificity of ± 1.4%. Assuming a one-year combined prevalence of disease equals to 4.2% in the transplant population, a total of 1208 patients will again yield a total of 51 cases and 1157 non-cases, giving a maximum 90% confidence interval width for specificity of ± 1.5%.

Across all 3 groups, a total of 4133 participants are required over a 5-year screening period. Assuming a participation rate of 68%, a population size of 6077 CKD patients is required to achieve the target sample size of 4133 for any meaningful analyses.

These sample sizes will provide 80% power to detect a difference of between 3% and 4% in specificity between groups of patients. The small number of expected cases does not allow comparisons in sensitivity to be made between groups.

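### The 51 cases and the ±10% precision for sensitivity assume that all disease is confirmed; under the planned verification, sensitivity for the combined endpoint is likely to be biased upward

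*Protocol article*

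**What the plan says.** All places are in the Protocol article, Study design 1.

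- *Statistical analyses and sample size calculations*: for each of the three groups, "the sensitivity is expected to be 75% and the maximum required 90% confidence interval width is ± 10" percentage points. The paragraph continues: "Therefore, 51 cases of advanced neoplasms and cancer will be required". Group sizes follow from prevalence. For CKD stages 3-5 ("with a one-year combined estimated prevalence of disease equals to 3.1"%), "a total of 1637 patients would yield 51 cases and 1586 non-cases". For dialysis ("with a one-year combined prevalence of disease equals to 3.94"%), "a total of 1288 patients would yield 51 cases and 1237 non-cases". The transplant group (4.2%) needs 1208. The total is 4133, raised to 6077 for 68% participation in screening. No other allowance is made.
- *Diagnostic procedures*: "All participants with positive iFOBT screens will be invited to undergo subsequent diagnostic colonoscopies". No colonoscopy is described for participants who screen negative.
- *Reference standard*: everyone is followed clinically for two years. Linkage to the state cancer registry at 2, 5 and 7 years is meant to pick up cancer diagnoses.
- *Outcomes*: the denominator of sensitivity includes both cancers and advanced neoplasms that come to light after a negative screen.

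**The concern.** The sample size paragraph and the verification scheme do not fit together. Dividing the required cases by prevalence makes every diseased participant an observed case. Yet the only procedure that reliably finds advanced neoplasia, colonoscopy, is offered only after a positive screen. A missed cancer can reach the registry. A missed advanced adenoma has no described route to detection unless it happens to be found in ordinary care.

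This matters because the precision of sensitivity is the basis for the group sizes, and so for 4133 and 6077. The sensitivity estimate also feeds the economic model (Study design 2), where an inflated value makes screening look better than it is. The Background raises the possibility that antiplatelet use increases test sensitivity in CKD. A value well above 75% that came only from incomplete verification could be read as support for that idea.

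**Working it through.** **1. The plan's own figures reproduce.** With sensitivity 0.75, half-width 0.10 and a two-sided 90% interval (z = 1.645), cases = 1.645² × 0.75 × 0.25 / 0.10² = 50.7, rounded up to 51. Group sizes: 50.73/0.031 = 1637; 50.73/0.0394 = 1288; 50.73/0.042 = 1208; sum 4133. Then 4133/0.68 = 6077.9 (stated as 6077).

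**2. Split of the 51 by screening result.** Screen-positive: 51 × 0.75 = 38.25. Screen-negative: 51 × 0.25 = 12.75.

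**3. Confirmed cases.** Let u be colonoscopy uptake among screen-positives and f the share of screen-negative disease that follow-up finds. The article gives neither, so both are assumptions.

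- Confirmed cases = 51 × 0.75 × u + 51 × 0.25 × f
- Apparent sensitivity = 0.75u / (0.75u + 0.25f)
- Wald 90% half-width = 1.645 × √(p(1 − p)/n), with p the apparent sensitivity and n the confirmed cases

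Example, u = 1 and f = 0.3: 38.25 + 3.825 = 42.1 cases; 38.25/42.075 = 90.9%; half-width 1.645 × √(0.909 × 0.091/42.075) = 7.3 points.

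| u | f | Confirmed cases | Apparent sensitivity | Half-width (points) |
|---|---|---|---|---|
| 1 | 1 | 51.0 | 75.0% | 10.0 |
| 1 | 0.5 | 44.6 | 85.7% | 8.6 |
| 1 | 0.3 | 42.1 | 90.9% | 7.3 |
| 1 | 0.1 | 39.5 | 96.8% | 4.6 |
| 1 | 0 | 38.3 | 100% | 0 (degenerate) |
| 0.8 | 1 | 43.4 | 70.6% | 11.4 |
| 0.8 | 0.5 | 37.0 | 82.8% | 10.2 |
| 0.8 | 0.3 | 34.4 | 88.9% | 8.8 |
| 0.8 | 0 | 30.6 | 100% | 0 (degenerate) |

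Only the first row gives the stated 51 cases and ±10 points.

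**4. Direction of the bias.** Apparent sensitivity exceeds 75% when 0.75u > 0.75 × (0.75u + 0.25f), that is, when u > f. The bias is upward whenever screen-positive disease is confirmed more completely than screen-negative disease. The verification scheme points that way.

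**5. Does the interval still cover the truth?** At u = 1, f = 0.3 the lower limit is 90.9 − 7.3 = 83.6%. At u = 0.8, f = 0.3 it is 88.9 − 8.8 = 80.1%. Both exclude 75%.

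**6. Specificity is hardly touched.** In the CKD 3-5 group, 0.90 × 1586 = 1427.4 true negatives. If all 12.75 missed cases are counted as disease-free, (1427.4 + 12.75)/(1586 + 12.75) = 90.1%.

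**The case against.** Several points on the other side stand.

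- **There is no arithmetic error.** Every figure checked in step 1 reproduces. The fault is an unstated assumption of complete ascertainment.
- **A reader might infer that 30 to 42 cases is a ceiling.** The documents do not support that. The range depends on assumed u and f, and wider assumptions (u down to 0.7, f from 0 to 1) run from about 27 to 51. Clinical follow-up also covers screen-positives who decline colonoscopy, and incident cancers can add to the count. The article does not say whether its one-year combined prevalence means true or clinically detected disease. If it means detected disease, part of the shortfall disappears. Nor does it give the split between cancer and adenoma.
- **A reader might infer that the precision simply worsens to ±11 to ±13 points.** Those are half-widths at 75% with 42 down to about 30 cases. When the lost cases are mainly screen-negative, the observed proportion is not 75%, and the reported interval is usually narrower than ±10 points around a value that is too high.
- **A reader might object to the word maximum, because 51 is only an expected count.** Even with perfect ascertainment the chance of reaching 51 is about 0.505 per group. But sizing on an expected count is conventional, the paragraph speaks of expected prevalence and expected cases, and for sensitivity the phrase reads as a design requirement. This is minor.

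None of this supplies a way to find advanced neoplasia in participants who are not scoped, so the central point remains.

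**Conclusion.** The concern holds as a mismatch between the sample size paragraph and the verification scheme. Fifty-one confirmed cases and ±10 points around 75% are best-case figures. On the plan's own inputs they need full colonoscopy uptake and full detection of disease after a negative screen, and no described procedure provides the second. About 38 of 51 per group are expected to screen positive; that figure needs no outside assumption.

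Under the illustrative u = 0.8 to 1.0 and f = 0 to 0.3, about 31 to 42 cases are confirmed and apparent sensitivity is about 89% to 100% against a true 75%. The upward bias, with an interval that looks precise and can exclude the truth, is the main consequence; the smaller case count comes second. The size rests on the assumed u and f, and the direction on u exceeding f. The group sizes need not change, and the specificity target is essentially unaffected.

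**What to change.** Keep the sample size and rewrite the sample size paragraph as follows.

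1. Describe 51 per group as the expected number of participants with disease, of whom about 38 are expected to screen positive.
2. Give expected confirmed cases as 51 × 0.75 × u + 51 × 0.25 × f over a stated range, with u and f labelled as assumptions.
3. Withdraw the ±10% claim for sensitivity to the combined endpoint. Present that sensitivity as likely biased upward, with a sensitivity analysis over f.
4. Rest the sensitivity claim on cancer, which the linkage can ascertain, and state its precision. It will be lower than for the combined endpoint, because cancers are only part of the 51. The article gives no split, so the authors must supply the figure.
5. Optionally, add positive predictive value among participants who have colonoscopy, which the design can estimate. With full uptake, positives are 38.25 + 0.10 × non-cases = 197, 162 and 154 (CKD 3-5, dialysis, transplant). Predictive values are 19.4%, 23.6% and 24.8%, with 90% half-widths of ±4.6, ±5.5 and ±5.7 points. These widen by 1/√u; at an assumed u = 0.8 they are ±5.2, ±6.1 and ±6.4. This quantity is not among the listed outcomes and would be an addition.

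The cost is one rewritten paragraph and one added analysis, with no extra patients and no change in procedures. The price is that the stated precision and the claim about sensitivity become less favourable.
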